#### **9.2.1.2 Secondary Analysis of Primary Endpoint**

The analyses for the primary endpoint for the pooled analysis will be repeated for participants who received two SDs of vaccine (ie, SDSD Seronegative for Efficacy analysis set).

#### **9.2.1.3 Subgroup Analysis of Primary Endpoint**

Subgroup analysis will be performed for the primary efficacy endpoint, the incidence of SARS-CoV-2 virologically-confirmed COVID-19. Within each level of a subgroup, the VE and its corresponding  $(1-\alpha)$  % CI will be estimated using a Poisson regression model with robust variance with the term of treatment. A forest plot of the VE and the  $(1-\alpha)$  % CI will be presented. If the Poisson regression model does not converge for any stratum of a subgroup, the exact conditional method for stratified Poisson regression using PROC GENMOD with the exact statement will be used.

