| Other                          | 02Nov2020 | Analysis sets were renamed/modified; overview of analysis was added in the appendix; redefined strategy for subgroups; AESI listing was replaced with updated definition in tables.                                                                                                                                              | Clarify the analysis planned. Update according to new information.                                                                                     |
| Other                          | 03Nov2020 | Remove highlight in TOC; change version to 3.0 from 1.1 in title (skip version 2.0) to match with version in ANGEL. Correct the HIV group in COV002.                                                                                                                                                                             | Clean the file.                                                                                                                                        |
| Primary or secondary endpoints | 03Nov2020 | Update case definition of asymptomatic SARS-CoV-2 infection. Update the homogeneity test may be conducted and change the model of subgroup analysis.                                                                                                                                                                             | Provide the source of information and reduce parameters in model.                                                                                      |
| Primary or secondary endpoints | 11Nov2020 | Added appendix for pooling of solicited events. Clarified COVID-19 infection will be virologically confirmed. Clarified subgroup analyses will be performed for all endpoints, unless specified otherwise.                                                                                                                       | Clarification of the analyses planned.                                                                                                                 |

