## 4. POOLING OF DATA

Despite minor differences across the studies, there is sufficient consistency to justify the proposal for pooled analyses. Some of the differences were driven by input from investigators, funders, and local specificities. The design of studies to be pooled is summarised in [Table 1](#).

The four Oxford-sponsored studies COV001, COV002, COV003, and COV005 are blinded, randomised, controlled studies that were designed to provide robust evidence of efficacy and safety of the AZD1222 candidate vaccine. The designs are compared in Table 1.

All studies enrolled adults 18 to 55. In addition, Studies COV002 (UK, Phase II/III) and COV003 (Brazil, Phase III), have enrolled older adults in age escalation groups of 56 to 69 years of age and  $\geq 70$  years of age. Enrolment in COV001 was restricted to healthy adults. The other studies allowed the inclusion of people with underlying health conditions with the exception of severe and/or uncontrolled underlying disease. All studies excluded pregnant and breastfeeding women. The safety and immunogenicity of AZD1222 in adults with known HIV infection was specifically investigated in a small subset of participants in Studies COV002 and COV005).

Collection and assessment of data for capture of COVID 19 variables is performed in a consistent manner across the studies. All participants have good access to health care and cases of COVID 19 are detected through passive surveillance systems. A central, blinded adjudication committee is being used by all 4 studies to assess COVID-19 cases from all participants with SARS-CoV-2 virologically positive results. Each case is assessed by the adjudication committee and classified according to the WHO severity grading scale reproduced in [Table 2](#). The adjudicated results are used for the pooled analyses.

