## 4.1 Planned Analyses

The proposed primary and interim pooled analyses provide an opportunity to produce early and robust estimates of efficacy to support rapid decision making in the present conditions of

this public health emergency. One interim analysis and one primary analysis are planned as below:

The interim analysis will be triggered when 53 COVID-19 cases (SARS-CoV-2 virologically confirmed) that occurred  $\geq 15$  days post the second dose have been reported in participants who received SD/SD (as defined in [Table 4](#)) across the AZD1222 and control groups in pooled studies. This would provide 77% power for the 20% threshold to assume a true vaccine efficacy of 70%. The analysis will include participants who received two doses, with a SD as the second dose (ie, participants who received LD/SD or SD/SD). For an individual study to be included in the pooled analysis of efficacy, a minimum of 5 primary endpoint defined cases must be accrued. For COV002, only cases accruing in efficacy study groups will be included (groups 4, 6, 9, 10).

The primary analysis will be triggered when 105 COVID-19 cases (SARS-CoV-2 virologically confirmed) that occurred  $\geq 15$  days post the second dose have been reported in participants who received SD/SD (as defined in [Table 4](#)) across the AZD1222 and control groups. This would provide 90% power for the 20% threshold to assume a true vaccine efficacy of 60%. The analysis will include participants who received two doses, with the second dose being SD (ie, participants who received LD/SD or SD/SD). For an individual study to be included in the pooled analysis of efficacy, a minimum of 5 primary endpoint defined cases must be accrued. For COV002, only cases accruing in efficacy study groups will be included (groups 4, 6, 9, 10).

Gamma Alpha-Spending function is used to control the overall Type 1 Error at 5%. The planned alpha level is 1.13% for interim analysis and 4.44% for primary analysis. The minimum observed VE if an interim or primary analysis demonstrates evidence of efficacy is 64% and 48%, respectively.

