## 9.2.1 Primary Efficacy Analyses

### 9.2.1.1 Pooled Analysis of Primary Efficacy Endpoint

A Poisson regression model with robust variance (Zou 2004) will be used as the primary efficacy analysis model to estimate the relative risk (RR) of the incidence of SARS-CoV-2 virologically-confirmed primary symptomatic COVID-19 between the AZD1222 and control groups. The model contains the term of study code, treatment group, and age group at randomization (ie, 18-55 years, 56-69 years, and  $\geq 70$  years). The logarithm of the period at risk for primary endpoint for pooled analysis will be used as an offset variable in the model to adjust for volunteers having different follow up times during which the events occur.

Vaccine efficacy (VE), which is the incidence of infection in the vaccine group relative to the incidence of infection in the control group expressed as a percentage, will be calculated as  $VE = 1 - \text{relative risk}$ . The VE, and its corresponding 2-sided  $(1-\alpha)$  % confidence interval (CI), will be estimated from the model. In addition, the 2-sided p value testing null hypothesis that the incidence of SARS-CoV-2 virologically-confirmed primary symptomatic COVID-19 between AZD1222 and control groups are the same will be obtained from the model. Statistical significance will be achieved if the 2-sided p value is  $\leq \alpha$ , where  $\alpha$  for interim and primary analysis as described in Section 4.1.

The Poisson regression with robust variance analysis will be implemented by using the SAS PROC GENMOD procedure for binary data with the REPEATED statement for subject ID and logarithm link. The estimated parameter  $\hat{\beta}$  [ie,  $\log(\widehat{RR})$ ], 2-sided  $(1-\alpha)$  % CI for  $\hat{\beta}$ , and the 2-sided p value will be obtained from the SAS outputs. The estimated RR and corresponding CI for the RR is given by exponentiating  $\hat{\beta}$  and its confidence limits. Therefore, the percent of VE is given by  $[(1 - \exp(\hat{\beta})) * 100\%]$ . The CI for the percent of VE is given by  $[(1 - \exp(\text{upper confidence limit for } \hat{\beta})) * 100\%, [1 - \exp(\text{lower confidence limit for } \hat{\beta})) * 100\%]$ .

If the Poisson regression model with robust variance fails to converge, the exact conditional method for stratified Poisson regression using PROC GENMOD with the exact statement will be used.

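### The subgroup model omits the study term that the overall model carries, so subgroup levels spanning several studies lose the within-study comparison; a cheap safeguard, not a demonstrated bias

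*SAP*

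**What the plan says.** For the overall estimate, SAP Section 9.2.1.1 specifies a Poisson regression with robust variance: "The model contains the term of study code, treatment group, and age group at randomization". The logarithm of the period at risk "will be used as an offset variable in the model to adjust for volunteers having different follow up times".

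For subgroups, Section 9.2.1.3 says that VE within each level will be "estimated using a Poisson regression model with robust variance with the term of treatment". Study code and age group are gone, and the offset is not restated. If a level does not converge, "the exact conditional method for stratified Poisson regression using PROC GENMOD with the exact statement will be used". No stratum is named.

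The amendment history records a change to the subgroup model and gives as part of its rationale to "reduce parameters in model". The simplification was therefore deliberate.

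On the make-up of the pool, Section 4 says: "The four Oxford-sponsored studies COV001, COV002, COV003, and COV005 are blinded, randomised, controlled studies". Section 4.1 adds an entry rule for each study: "a minimum of 5 primary endpoint defined cases must be accrued". Section 7.2 lists age, country, comorbidity and baseline serostatus as subgroups. It adds others that may be explored, dose schedule among them.

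**The concern.** The randomised comparison exists only inside each study. A model with treatment alone adds up the vaccine arms and the control arms across studies and compares the totals. If one study contributes relatively more vaccine person-time than another and the two have different incidence, part of the difference between studies passes into the treatment effect. Robust variance corrects the standard error and does nothing about this.

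The SAP gives reasons to expect incidence to differ. Table 1 places the studies in three countries, with different exposure profiles: COV003 enrols health professionals and adults at high risk of exposure, COV001 healthy adults aged 18 to 55. Section 4 says that COV002 adds weekly self-swabs and COV005 swabs or saliva at scheduled visits.

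The rest of the SAP treats study or country as something to adjust for. Section 9.2.2.1 removes study code only for an endpoint confined to COV002. The supportive Cox model in Section 9.2.1.4 is stratified by age group and country. Section 9.2.2.3 applies the full overall model to the remaining secondary endpoints once 5 cases have accrued.

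At stake are the estimates for older adults and for people with comorbidity. According to Section 4 and Table 1, participants aged 65 and above come essentially from COV002 and COV003, so that level mixes a UK and a Brazilian trial if both qualify.

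**Working it through.** The SAP states no figure for the subgroup analysis. Its power figures in Section 4.1 concern the overall analysis and do not depend on this point.

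**Formula.** Suppose VE is the same in all studies. Study *s* has baseline rate λ_s, vaccine person-time V_s and control person-time C_s. Then

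crude RR = (1 − VE) × [Σ V_s λ_s / Σ V_s] ÷ [Σ C_s λ_s / Σ C_s].

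If V_s/C_s is the same in every study, whether 1:1 or not, the two bracketed averages are equal and the crude VE is correct whatever the rates.

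**Illustration.** Assumptions: two studies of 2,000 with equal follow-up, control attack rates 1% and 3%, true VE 60%, one study 1:1 and the other *r*:1.

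Worked case, *r* = 2 in the high-incidence study:
- Vaccine: 0.4 × (1,000 × 1% + 1,333.3 × 3%) = 20.0 cases in 2,333.3, or 0.857%.
- Control: 1,000 × 1% + 666.7 × 3% = 30.0 cases in 1,666.7, or 1.80%.
- RR = 0.476, so crude VE = 52.4%.

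Worked case, *r* = 2 in the low-incidence study:
- Vaccine: 0.4 × (1,333.3 × 1% + 1,000 × 3%) = 17.33 cases in 2,333.3, or 0.743%.
- Control: 666.7 × 1% + 1,000 × 3% = 36.67 cases in 1,666.7, or 2.20%.
- RR = 0.338, so crude VE = 66.2%.

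| *r* | Crude VE, high-incidence study unbalanced | Crude VE, low-incidence study unbalanced |
|---|---|---|
| 1 | 60.0% | 60.0% |
| 1.25 | 57.7% | 62.2% |
| 1.5 | 55.7% | 63.8% |
| 2 | 52.4% | 66.2% |

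**Planned study sizes.** Table 1 plans 1,122, 12,390, 10,000 and 2,070 participants. Assume all studies are 50% active except COV002, that UK and non-UK rates differ 2-fold in either direction or are 4-fold higher outside the UK, and a true VE of 60%:
- COV002 50% active: crude VE 60.0% in every case.
- COV002 60% active: 57.5% to 64.3%.
- COV002 67% active: 55.6% to 67.0%.

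**Simulation.** Same study sizes and scenarios plus equal rates, 105 expected cases, 600 runs each, leaving out runs in which a study had no cases. With study in the model, mean VE stayed between 59.8% and 60.8% and coverage of the 95% interval between 94.1% and 97.5%. With treatment only, coverage fell to 85.1% in the worst scenario (COV002 67% active, 4-fold higher rates outside the UK). In that scenario the mean standard error of log RR was 0.212 without study and 0.214 with it. With equal allocation the two models gave the same results.

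**The case against.** The strongest objection is that no bias is shown. The SAP gives neither allocation ratios nor attack rates, so every unequal scenario above is an assumption. The one relevant count is in Section 1.2: 544 of 1,077 COV001 volunteers, 50.5%, received at least one standard-level dose of AZD1222, which points to balance in that study. Table 3 carries the corresponding control group along with each dose regimen, which limits the imbalance that selection by dose could create. This stands, and it sets the strength of the conclusion.

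The simplification also has a reason. Cases split across subgroup levels may leave a study with none in a level, and the simulation, run at 105 expected cases without such runs, does not test that. The sparsity concern is fair, but conditioning on study meets it without estimating a parameter for each study.

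The possible shift is also small beside subgroup uncertainty. For an assumed level with 30 cases, 1:1 person-time and VE 60%, the split is 30 × 0.4/1.4 = 8.57 vaccine and 21.43 control cases. SE(log RR) = √(1/8.57 + 1/21.43) = 0.40, and the 95% interval is about 12% to 82%. That is true, but imprecision is no reason to accept an avoidable systematic error as well. Section 7.2 describes the subgroups as exploratory, which limits the consequence.

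A reader might infer three stronger things that the SAP does not support:
- That the subgroup estimates will sit beside the study-adjusted overall VE on one plot. Section 9.2.1.3 promises "A forest plot of the VE and the" confidence interval and does not say that the overall estimate is included.
- That four trials are mixed in every subgroup. Brazil and South Africa are single-study levels, and the 5-case rule may remove studies.
- That the fallback is wrong. The unnamed stratum and the unstated offset are gaps in wording; without a stratum, the method reduces to an unstratified exact fit.

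**Conclusion.** The inconsistency is real: the subgroup model drops the study term that the overall model carries, although subgroup levels such as age and comorbidity span separately randomised studies. Whether this biases anything cannot be settled from the SAP. Under the assumed 1% and 3% attack rates and true VE of 60%, the error is about 2 points at 1.25:1 in one study, 4 points at 1.5:1 and 6 to 8 points at 2:1. It is zero when vaccine:control person-time has the same ratio in all studies. The change is worth making as a safeguard: it analyses people within the groups in which they were randomised and, at 105 cases, costs almost no precision. It is a minor point.

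**What to change.** In Section 9.2.1.3, for every subgroup level that spans more than one study, stratify by or condition on study, or keep study code as a covariate. State that the log period-at-risk offset is kept, and name study as the stratum of the exact conditional fallback. Only the age term need be dropped. Single-study levels (Brazil, South Africa) can stay as they are.

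The cost is one model term and a sentence or two of text. Levels in which a study has few or no cases will need the conditional or exact fit more often, and a study with no cases in a level contributes nothing to that estimate.

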#### **9.2.1.4 Supportive Analyses for Primary Efficacy Endpoint**

To support the primary analysis, a Cox Proportional Hazards model using the same covariates as for the primary analyses as well as Kaplan-Meier curves will be presented for the active and control groups based on observed events, showing the cumulative incidence of the first case of SARS-CoV-2 RT-PCR-positive symptomatic illness occurring  $\geq 15$  days post second dose of study intervention. Time to event, i.e., the duration in days since 15 days post second study dose to event or censoring, will be fit using the PH model with treatment as a factor and age group, country as stratum. Hazards ratios for each study arm along with the two-sided  $(1-\alpha)$  % CI will be obtained from the PH model. The number of participants with a primary endpoint and the number of censored participants will also be provided. The censoring timing at each month will be displayed.

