### 1.2 Clinical Experience with AZD1222

The University of Oxford is investigating the safety, immunogenicity, and efficacy of AZD1222 in 3 ongoing meningococcal vaccine-controlled clinical studies: a FIH Phase I/II Study COV001 in healthy adults 18 to 55 years of age in the UK; a Phase II/III Study COV002 in healthy adults  $\geq 18$  years of age (including the elderly) and children 5 to 12 years of age in the UK; and a Phase III Study COV003 in healthy adults  $\geq 18$  years of age in Brazil. An additional Phase I/II study using a saline placebo control, COV005, is ongoing in South Africa. For these studies, AZD1222 CTM from 3 different sources has been used: 1) The CBF at the University of Oxford; 2) Advent, Italy, and 3) Cobra Biologics. The analytical comparability assessment of AZD1222 Process 1 (CBF), Process 2 (Advent), and Process 3 (Symbiosis) for the clinical Drug Product, was conducted. Due to a potency miscalculation, participants in Groups 1, 2, 4 and 5a in Study COV002 received a lower dose of approximately  $2 \times 10^{10}$  vp instead of the planned dose of  $5 \times 10^{10}$  vp. Groups receiving this lower dose are listed as having received  $5 \times 10^{10}$  vp (Abs260) Advent in the study protocols.

The complete list and description of these ongoing University of Oxford-sponsored AZD1222 clinical studies is presented in [Table 1](#).

Emerging safety and immunogenicity data from all the Oxford sponsored studies are reviewed approximately every 2 weeks by an independent DSMB. Preliminary safety and

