ECMO = extracorporeal membrane oxygenation; FiO2 = fraction of inspired oxygen; NIV = non-invasive ventilation; pO2 = partial pressure of oxygen; SpO2 = oxygen saturation.

Source: (WHO et al 2020).

Case definitions for the pooled analysis are given in Table 6. Per protocol in UK studies ICU admission was a protocol defined endpoint. In order to standardise “ICU admission” across trials for differences in local medical practice, this was redefined as “Requiring ICU admission” and corresponds to those WHO severity grades reflecting the need for mechanical ventilation.

Studies COV001, COV002, COV003, and COV005 are all randomised, controlled studies in healthy volunteers with similar efficacy endpoints. Case detection methods for efficacy assessments are also similar. Access to care for passive case detection is available in all studies; COV002 also includes weekly self-swabs for detection of infection and COV005 includes nasal swab and/or saliva on each scheduled visit. Key inclusion criteria are similar for all studies, except for age. Although there are some differences in the exclusion criteria across the studies, study populations are generally similar. All studies excluded patients with serious conditions or receiving medication that could interfere with the study conduct or the interpretation of study data.

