## 7.2 Definitions of Subgroups

To explore the implications for efficacy, safety, and immunogenicity among different populations, the following subgroups will be used:

- Age at randomization;
  - 18-64, 65 years and above
  - 18-55, 56-69, 70 years and above (for efficacy analysis of the primary manuscript only)
- Country (UK, Brazil vs South Africa)
- Comorbidity at baseline (at least one comorbidity vs no comorbidity), where comorbidity is BMI  $\geq 30$  kg/m^2 at baseline, Cardiovascular Disorder, Respiratory disease or Diabetes.
- Baseline serostatus (seronegative vs seropositive)

The analyses by each subgroup will be performed for all endpoints (efficacy, safety, and immunogenicity) unless specified otherwise.

Additional subgroups which may be explored include but are not limited to:

- Gender (male, female)
- Race (Asian, Black, White, Mixed, Other, Unknown): only categories with at least 100 individuals exposed will be presented
- Use of prophylactic paracetamol (for analysis of reactogenicity)
- Dose level (LD/SD vs SD/SD)
- Dose schedule (< 6 weeks, 6-8 weeks, 9-11 weeks,  $\geq 12$  weeks)
- Control type (MenACWY, Saline) (for safety only)

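### SAP Section 9.2.1.4 specifies the supportive Cox model in two incompatible ways, adjusting by study code or stratifying by country, and should state one

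*SAP*

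**What the plan says.** Section 9.2.1.4 describes the supportive analysis twice. The opening sentence promises "a Cox Proportional Hazards model using the same covariates as for the primary analyses". The primary model is defined in Section 9.2.1.1: "The model contains the term of study code, treatment group, and age group at randomization", with age in three groups (18-55, 56-69, 70 and over). The next sentence of Section 9.2.1.4 says that time to event "will be fit using the PH model with treatment as a factor and age group, country as stratum".

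Section 7.2 gives country three levels: UK, Brazil and South Africa. Table 1 lists four studies, of which COV001 and COV002 are both in the United Kingdom. Section 4 (text after Table 2) states that "Studies COV001, COV002, COV003, and COV005 are all randomised, controlled studies in healthy volunteers", so each of the two UK studies is a trial in its own right. Section 4.1 admits a study to the pooled efficacy analysis only once it has at least five primary endpoint cases.

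**The concern.** The two sentences differ in two respects. Study code is replaced by country, and age group changes from a model term to a stratum. Two programmers could each follow the section and report different hazard ratios, although the analysis is meant to be prespecified.

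The choice is not purely verbal, because country is coarser than study. The country version puts COV001 and COV002 under one baseline hazard, and the SAP itself shows that they differ:

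- **Start:** 23 April against 29 May 2020 (Table 1). The time axis runs from 15 days after the second dose, not from a calendar date, so the same analysis day can fall in different phases of the epidemic.
- **Population:** healthy adults aged 18-55 in COV001. COV002 takes adults of 18 and over, gives priority to health professionals and people with high exposure (Table 1), and allows underlying conditions (Section 4).
- **Swabbing:** "COV002 also includes weekly self-swabs for detection of infection", which Section 4 does not list for COV001.

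The Cox model is there to support the Poisson result. If the adjustment set changes along with the method, a difference between the two results is harder to read.

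**Working it through.** **Wording.** The SAP gives no figure to reproduce here, so the check starts with the text.

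| | First sentence of 9.2.1.4 (via 9.2.1.1) | Second sentence of 9.2.1.4 |
|---|---|---|
| Treatment | model term | factor |
| Study code | model term | absent |
| Country | absent | stratum |
| Age group | model term | stratum |

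Combining the two (study code as covariate, country as stratum) does not rescue the text. Age group would then be both covariate and stratum, and the second sentence names treatment as the only factor.

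**Levels.** With all four studies in, there are 4 study codes and 3 countries, so nominally 4 × 3 = 12 against 3 × 3 = 9 cells with age group. By the age ranges in Table 1, COV001 fills one age group (18-55), COV002 and COV003 three each, and COV005 (18-65) two. That is 1 + 3 + 3 + 2 = 9 populated cells by study and 3 + 3 + 2 = 8 by country. The two versions differ in one cell only: UK, ages 18-55. If COV001 misses the five-case minimum, study and country coincide (three of each for COV002, COV003 and COV005).

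**Effect of the merge.** Let w be COV001's share of UK person-time, a1 and a2 the vaccine shares in COV001 and COV002, k the COV001:COV002 incidence ratio, and RR the true relative risk. The crude relative risk in the merged UK data is

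RR × [(w·a1·k + (1−w)·a2) / (w·a1 + (1−w)·a2)] ÷ [(w·(1−a1)·k + (1−w)·(1−a2)) / (w·(1−a1) + (1−w)·(1−a2))].

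If a1 = a2 the two brackets are equal and RR is unchanged for any k. If k = 1 both brackets are 1. A shift therefore needs both allocation and incidence to differ.

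The SAP gives no allocation ratio or incidence for the seronegative two-dose participants, so the following are assumptions: RR = 0.4 (efficacy 60%), a1 = 0.5, w = 8% or 15%. Planned enrolment in Table 1 gives 1122 / (1122 + 12390) = 8.3%, but COV002's total includes groups outside the efficacy set.

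| a2 | k | w = 8% | w = 15% |
|---|---|---|---|
| 0.5 | 0.5 to 2 | 60.0% | 60.0% |
| 0.6 | 0.5 | 59.4% | 58.8% |
| 0.6 | 2 | 61.1% | 61.8% |
| 0.667 | 0.5 | 58.8% | 57.9% |
| 0.667 | 2 | 61.9% | 63.1% |

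One line in full (w = 0.15, a2 = 0.667, k = 2): vaccine bracket (0.150 + 0.567) / 0.642 = 1.117; control bracket (0.150 + 0.283) / 0.358 = 1.209; 0.4 × 1.117 / 1.209 = 0.369, so efficacy is 63.1%.

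These are UK figures, whereas Section 9.2.1.4 estimates a pooled hazard ratio. With planned enrolment as a rough weight, the UK is 13512 / 25582 = 53%. The largest shift, 3.1 points, then becomes about 3.1 × 0.53 = 1.6 points.

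**The case against.** The strongest reply is that nothing depends on this. Significance is judged on the Poisson model, which contains study code, and the Cox model has no success criterion. The second sentence can be read as the operative specification, and country is a reasonable stratum that Section 7.2 already uses as a subgroup factor. COV001 may also never enter the pool.

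Most of this stands, and it keeps the point minor. It does not remove the conflict: if the second sentence governs, the first is wrong about study code. Country is also the exception in this plan. The five-case rule (Section 4.1), the primary model and the homogeneity test (both Section 9.2.1.1) all work by study. Since each study lies within one country, stratifying by study loses no adjustment for country.

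A reader might infer that merging the UK studies materially biases the supportive estimate. The SAP does not support that. Its only allocation figure for COV001, in Section 1.2, is 544 of 1,077 volunteers given AZD1222, or 50.5%, close to 1:1. That is enrolment, not the analysis set, but the unequal ratios in the table above have no source in the document.

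A reader might also think that the UK studies differ in their number of two-dose groups. Table 1 describes both identically, as one or two doses depending on group.

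**Conclusion.** The point holds as an inconsistency in a supportive analysis. Section 9.2.1.4 gives two models that cannot both be fitted, and the SAP does not say which applies. That is so whatever data accrue.

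The merge of COV001 and COV002 is conditional. It needs COV001 to reach five cases and touches only the UK 18-55 stratum. It moves the estimate only if allocation and incidence both differ between the two studies. The likely effect is small and may be nil. Shifts of about 1 to 3 points in the UK data arise only under the assumed imbalances shown. The ratio that would settle the matter, among seronegative two-dose participants, is not in the SAP. The primary efficacy result and its significance test are unaffected.

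**What to change.** State one Cox specification in Section 9.2.1.4: treatment as factor, stratified by study code and age group. Replace country by study code in the second sentence. Reword the first to say that the primary model's adjustment factors, study code and age group, enter as strata. The Cox model will then use the same factors as Section 9.2.1.1 and follow the units of randomisation. It will not be identical to the Poisson model, because strata allow a separate baseline hazard per cell where the Poisson model has additive terms on the log scale. If country is intended, the SAP should say so and give the reason.

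The cost is two edited sentences and one changed stratification variable in the program. At most one populated stratum is added.
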